#### ​Incident and prevalent users

Exposure status will be defined at cohort entry as

‘No OAC’, where the patient had at least a year free of OAC prior to study entry and does not receive an OAC during the study period.‘Incident OAC users’, where the patient had at least a year free of OAC prior to study entry then was prescribed an OAC during the study period.‘Prevalent OAC users’ if the patient received an OAC in the year prior to study entry.

Exposure status for incident OAC users will be stratified at the start of each study period to no OAC, warfarin or DOAC.

#### ​Indication for prescribing

OACs are prescribed for many different indications, but only those prescribed for stroke prevention in AF will be included in this study. Patients will be excluded from the study if

They had a hip fracture or hip replacement in the 6 weeks prior to the OAC index date and only one prescription for an OAC.They had a venous thromboembolism in the 6 months prior to the OAC index date.

#### 
*​*DOAC prescription duration

The index date will be defined as the date the first prescription was issued. The expected end date will be calculated by dividing the number of tablets prescribed by the licensed number of doses per day (ie, two doses per day for dabigatran and apixaban and one dose per day for rivaroxaban and edoxaban). Where the quantity of tablets prescribed is not specified, the expected duration will be imputed from other prescriptions issued for the same product for that patient or overall for that product if patient-specific information is not available.

Patients will be classified as being continuously exposed until there is a gap of >60 days between the expected end of one prescription and the start of the next. Where there is a gap of ≤60 days between the expected end of one prescription and the start of another for the same DOAC (regardless of whether the strength prescribed changes), the gap will be filled and defined as continuous exposure. Where a subsequent prescription for the same product is issued before the expected end of the previous prescription, the prescriptions will be concatenated and the extra days will be added to the expected end date of the second prescription. A maximum of 60 additional days will be allowed per patient.

A DOAC will be defined as discontinued 60 days from the expected end date of the last prescription issued for that product.

#### 
*​*Warfarin prescription duration

Warfarin does not have a fixed dosing schedule; the dose is amended based on the results of a blood test, the international normalised ratio (INR). In the UK, patients are issued with different strength tablets (0.5, 1.0, 3.0 and 5.0 mg) and are advised, following each INR test, what dose they need to take and what strength of tablets to use. Dosing information for warfarin is not recorded in the CPRD; however, the strength and quantity of warfarin tablets issued by the general practice are recorded. Read codes for warfarin monitoring and results of INR tests are also recorded by some general practices, but this is not recorded consistently.

The index date will be defined as either the date of the first prescription issued or from the date of the first INR test result above 2 if this occurs before the first issue of a prescription. Patients may be exposed to warfarin before the first prescription issued by their GP if treatment is started in the hospital. CPRD data do not include hospital prescribing; hence, INR test results of ≥2 will be used as a surrogate marker of exposure.

The expected end date for warfarin prescriptions will be estimated using the median time between all previous prescriptions issued to the same patient. For example, if four prescriptions had been issued for 28×1 mg tablets and the gaps between the prescription issue dates were 15, 35 and 42 days, we would define the final prescription for 28 tablets as lasting 35 days, so the expected end date of the last prescription would be 35 days from the issue date. Where multiple strengths are issued for a patient, the median will be calculated for each strength and the expected end date will be the latest of these dates.

If only one prescription has been issued, the expected end date will be assumed to be equal to the median warfarin prescription gap for the cohort.

A patient will be assumed to have discontinued warfarin treatment if there is a period ≥2 times their median prescription gap. If an INR test result of ≥2 is recorded in the discontinuation period (expected end date of the last prescription to the date equal to twice their median prescription gap), then INR tests will be used as a surrogate marker for warfarin prescribing and the end date will be defined as 1 week following the final INR test result of ≥2.

The procedure for warfarin mapping is illustrated in figure 1. This will be repeated for each strength and the patient classed as unexposed from the latest discontinuation date of all the strengths.

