## Introduction

A large body of evidence has shown that vitamin K antagonists (VKAs) are safe and effective for stroke prevention in atrial fibrillation (AF), but they have frequently been underused in older people.^1^ Reasons cited by physicians as making them less likely to prescribe VKAs for a person with AF include advancing age, risk of falls, comorbidities and previous bleeding.^2^

The first direct oral anticoagulant (DOAC), dabigatran, was marketed throughout Europe and in the UK in 2008, but was not licensed for stroke prevention in AF until 2011. Since then, three additional DOACs have been licensed for prevention of stroke: rivaroxaban, apixaban and edoxaban, and these are recommended in national and international guidelines as an alternative to warfarin.^3–5^ In the UK, the National Institute of Clinical Excellence (NICE) produces technology appraisals making recommendations for new medicines. The National Health Service is legally obliged to fund those medicines recommended by NICE within 3 months of publication of the appraisal. NICE published favourable technology appraisals for dabigatran and rivaroxaban in 2012,^6 7^ apixaban in 2013^8^ and edoxaban in 2015,^9^ meaning DOACs were available across the UK from mid-2012 onwards for stroke prevention in AF.

DOACs may allay some prescribers’ concerns when deciding whether to anticoagulate their older patients: they have fixed dosing schedules and can be added to compliance aids. They have also been shown in clinical trials to have a significantly lower risk of intracranial haemorrhage than warfarin^10–13^ (a prominent concern in patients with a history of falls).^14^

Since the introduction of DOACs, the overall rate of oral anticoagulant (OAC) initiation has increased by 58%.^15^ However, it is not known whether the introduction of DOACs has changed the rates of OAC prescribing for older people (aged ≥75 years) or how patient demographics, comorbidities and concomitant prescribing affect the choice of anticoagulant prescribed in UK general practice.

This study aimed to characterise prescribing of OACs to people aged ≥75 years in UK general practice, before and after the introduction of DOACs.

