### Time periods

The cohort will be analysed in three time periods:

Period 1: prior to the introduction of DOACs (2003–2007).Period 2: during the period between the introduction of DOACs and the time they were recommended by NICE (2008–2012).Period 3: following the publication of the NICE technology appraisals recommending DOACs as an option for stroke prevention in AF (2013–2017).

For each time period, patients will contribute data to either the warfarin, DOAC or no OAC group. Patients in the cohort can contribute data to more than one time period and more than one group, and may contribute differently for each objective. Patients may only contribute to the incident OAC group once with their index OAC. Any further prescriptions for different OACs would be considered to be prevalent.

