### Exposure

The OACs of interest in this study are warfarin, dabigatran, rivaroxaban, apixaban and edoxaban. Warfarin is the only VKA included as it is the most commonly used VKA in the UK. Dabigatran, rivaroxaban, apixaban and edoxaban are the only DOACs licensed for the prevention of stroke in AF available during the study period.

All prescriptions for the OACs of interest that are issued following an AF diagnosis, during the study period and in the year prior to entry in to the study cohort will be identified.

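### The two indication exclusions do not ensure that only AF prescribing is counted: pre-2011 DOAC issues and post-hip courses with more than one prescription can enter as AF initiations

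*Protocol article*

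**What the plan says.** Under Indication for prescribing, the protocol states that "only those prescribed for stroke prevention in AF will be included in this study". Two exclusions put this into practice:

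- "They had a hip fracture or hip replacement in the 6 weeks prior to the OAC index date and only one prescription for an OAC"
- "They had a venous thromboembolism in the 6 months prior to the OAC index date"

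The capture rule under Exposure is broad: "All prescriptions for the OACs of interest that are issued following an AF diagnosis, during the study period" (and in the year before cohort entry). The Abstract sets the exposure threshold at one prescription. Nothing restricts by licence date, recorded indication or a minimum number of issues.

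On the calendar, the Introduction says that the first DOAC, dabigatran, "was marketed throughout Europe and in the UK in 2008, but was not licensed for stroke prevention in AF until 2011", and adds: "Since then, three additional DOACs have been licensed for prevention of stroke". Time periods defines Period 2 as 2008–2012 and states: "Patients may only contribute to the incident OAC group once with their index OAC".

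Other rules decide what happens next. At-risk time ends at the first OAC prescription (Objective 1). A DOAC counts as discontinued 60 days after the expected end of its last supply (DOAC prescription duration). Any later issue of a different OAC is a switch (OAC switching). All incident users enter the persistence model (Objective 4).

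**The concern.** The stated intent is AF use only, but the rules that implement it are narrower than the intent in two places.

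**Pre-licence DOACs.** Period 2 starts when DOACs reached the market, not when one was licensed for AF. A DOAC issued to a cohort member in 2008–2010 passes the filter unless it follows a recent venous thromboembolism, or a recent hip event with no other OAC prescription. It then counts as an AF start, although by the protocol's own account it was either for something else or off-licence for AF.

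**The prescription count in the hip exclusion.** A post-hip course supplied as two prescriptions is kept. So is a single-prescription course in a patient who starts an OAC for AF much later, and then the index date is the surgical course. The rule depends on everything issued in the remaining follow-up, so two patients with identical surgical courses can be classified differently only because one was followed for longer.

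At stake are the Period 2 DOAC incidence and the profile of the newly started group (Objectives 1 and 3), the switch counts (Objective 2), and the DOAC-versus-warfarin persistence comparison (Objective 4). Because only one incident entry is allowed, a false start also removes a later true one.

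**Working it through.** The protocol gives no count of such prescriptions, so there is no figure to reproduce. The check traces the rules, then shows how the effect would scale.

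**1. Calendar** (Introduction, Time periods). Whole Period 2 years before any AF licence: 2008, 2009 and 2010, so 3/5 = 60%. The Introduction puts UK-wide availability for AF at mid-2012, so about 4.5/5 = 90% of Period 2 precedes that.

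**2. Rule trace for a cohort member with AF already diagnosed**

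| Case | Exclusion met? | How it is handled |
|---|---|---|
| Hip event within 6 weeks, one OAC prescription, none ever after | Yes | Patient removed |
| Same, course issued as two prescriptions | No | Incident start, then discontinuation |
| Same, one prescription, AF start years later on a different OAC | No | Index at surgical course; later start coded as a switch |
| Same, later AF start on the same OAC | No | Index at surgical course; individual review |
| DOAC issued in 2008–2010, no recent hip event or venous thromboembolism | No | Incident AF start |

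The individual review (Restarting index OAC after discontinuation) covers only restarts of the index product. It asks whether treatment had really stopped, not what it was for.

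**3. When a short DOAC course becomes a discontinuation.** Day = supply + 60, with supply lengths assumed:

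- one issue of 10, 14, 28 or 35 days: day 70, 74, 88 or 95
- two consecutive issues of 14 or 28 days: 2 × 14 + 60 = day 88, or 2 × 28 + 60 = day 116

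These are events at roughly two to four months in the Objective 4 model.

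**4. Scale.** Let c be the share of counted DOAC starts that are short non-AF courses, and S the true one-year persistence. Both are assumed. If every such course ends within the year:

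- observed persistence = S(1 − c)
- inflation of the start count = 1/(1 − c)
- apparent ratio of one-year cumulative hazards = ln[S(1 − c)] / ln S

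With S = 70%:

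| c | Observed persistence | Start count inflated by | Hazard ratio |
|---|---|---|---|
| 1% | 69.3% | 1.01 | 1.03 |
| 5% | 66.5% | 1.05 | 1.14 |
| 10% | 63.0% | 1.11 | 1.30 |
| 20% | 56.0% | 1.25 | 1.63 |

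Over S = 60–80% and c = 1–20% the ratio runs from 1.02 to 2.00. It compares contaminated with true DOAC persistence at one year and is not the Cox estimate. The inflation factor ignores later true starts that are lost. For Objective 4, c applies to all DOAC starts up to 2017; for Objective 1, to those in the year concerned.

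**The case against.** The case for leaving the rule alone has substance.

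- Every counted patient is at least 75 and has an AF code with supporting evidence, and the prescription must follow the AF diagnosis. This makes AF a plausible reason but does not establish it, and the protocol itself says OACs have many indications.
- CPRD holds no hospital prescribing (Warfarin prescription duration), so hospital-supplied courses never enter. This stands, and is the main reason the number may be small.
- Incidence is reported by year and by product, so odd pre-2011 starts would be visible. This stands for Objective 1 but not for Objectives 3 and 4, which work by period or pool all starts. In Objective 4, pooling to 2017 also dilutes any effect.
- The single-prescription condition protects AF patients who stay on an OAC after hip surgery. That aim is sound, but a time window serves it without depending on prescriptions issued years later.
- In a descriptive study, dropping every pre-licence start from the main analysis would discard genuine off-licence AF use. This stands, and is why a sensitivity analysis is preferable.

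A reader might infer that true AF use of DOACs before 2011 was near zero, so that all these starts are false. The documents do not support this: unlicensed use is not proof of non-AF use, and no proportion is given. A reader might also infer that they were prophylactic courses after some other operation, such as knee replacement. The protocol does not say what DOACs were licensed for before 2011, so that would rest on outside knowledge.

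**Conclusion.** The gap between the stated AF-only intent and the two exclusions is real, and confidence in it is high: it follows from the protocol's own text and dates. As written, the rules can count non-AF courses as AF starts, end at-risk time so that a later AF start is lost, and code the course as a discontinuation 60 days after supply ends or, if a different product follows, as a switch.

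The size is not established. The documents give neither the number of pre-licence DOAC issues nor their indication, and the scale figures rest entirely on assumed values of c and S. At c = 1% the distortion is negligible; it becomes material at around 5–10%. The pre-licence part falls on DOACs alone, but the hip part can affect warfarin too, so the text does not show that the persistence comparison is materially biased. The point supports a tighter rule and a sensitivity analysis, not a conclusion that the planned results would be wrong.

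**What to change.** Under Indication for prescribing:

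1. Replace the single-prescription condition with a time-window rule: a post-hip course is non-AF use if no further OAC is issued within a prespecified interval after its expected end. Define the course as all linked prescriptions, so that split supplies are caught, and prespecify its maximum length, so that patients who continue long term are kept. State how to classify a patient whose follow-up ends inside the window.
2. Do not let such a course set the index date, and leave the patient at risk for a later AF start.
3. Report DOAC starts before the 2011 AF licence separately. In a prespecified sensitivity analysis, repeat Objectives 1, 3 and 4 without counting them as AF initiations, keeping those patients at risk. The Introduction gives only the year, so the cut-off date must be stated.

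The cost is slightly more data preparation and one extra set of results. The main analysis keeps pre-licence starts, so no genuine off-licence AF use is lost from it.

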**Methods and analysis:**

A retrospective cohort study design will be used. Patients with a diagnosis of AF will be identified from the Clinical Practice Research Datalink (CPRD). The study period will run from 1 January 2003 to 27 December 2017. Patients enter the cohort at the latest date of the start of the study period, first AF diagnosis, 75th birthday or a year from when they started to contribute research standard data. Follow-up continues until they leave the practice, death, the date the practice stops contributing research standard data or the end of the study period (27 December 2017). Exposure to OACs will be defined as ≥1 prescription issued for an OAC of interest during the study period. Patients issued an OAC in the year preceding study entry will be defined as ‘prevalent users’. Patients starting on an OAC during the study period will be defined as ‘incident users’. Incidence and prevalence of OAC prescribing, patient demographics and characteristics will be described during three time periods: 2003–2007, 2008–2012 and 2013–2017. Persistence (defined as the time from initiation to discontinuation of medication) with and switching between different OACs will be described.

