## Discussion

A number of studies have described changes in anticoagulation prescribing in the time since DOACs were introduced in the UK.^15 27 28^ However, none have focused specifically on their use in older people aged ≥75 years, despite older people being the largest users of anticoagulants for AF. The main strength of this study is that it will investigate prescribing in a large cohort of older patients using the CPRD, which is generally representative of the UK population. This study will look at a number of different factors that may influence the prescribing of anticoagulants and how these have changed over time. The results of this study will inform future comparative studies between OACs as it will provide an insight to potential confounders which may need to be controlled for. A limitation of this study is defining accurately when patients are exposed to an anticoagulant and when they are not. This is particularly difficult for warfarin as dosing information is not included in the CPRD. A number of studies have compared DOACs and warfarin using routinely collected healthcare data, but they do not describe how they mapped warfarin exposure.^29 30^ This protocol is transparent in describing our planned method for warfarin mapping and uses both prescription and test result data. We will also investigate gaps in prescribing to establish whether patients may have been in the hospital or having their OAC prescribed elsewhere; this is likely to be more common in this age group than others and has been noted as a limitation in other studies.^31^ A second limitation is that comorbidities may not always be recorded in the CPRD, particularly where they are diagnosed and treated in secondary care. However, as the comorbidities we have chosen are chronic and likely to have a significant impact on patients’ health, it is likely that they would be recorded accurately. Finally, as it is difficult to predict whether prescriptions for concomitant medicines are still continuing at any given time, we have decided to assume that if a prescription was issued in the 3 months prior to an OAC being started, the concomitant medicine is still continuing at that time. This is likely to be the case as most medications of interest are for chronic conditions. However, we acknowledge that it may overestimate exposure to these concomitant medications.

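### Patients with repeated INR ≥2 but no GP anticoagulant prescription stay in the incidence denominator and the no-OAC comparison group, although the plan's own surrogate marks them as anticoagulated

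*Protocol article*

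**What the plan says.** All references are to the protocol article.

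- **Abstract, Methods and analysis.** The general definition is "Exposure to OACs will be defined as ≥1 prescription issued for an OAC of interest during the study period".
- **Incident and prevalent users.** A no-OAC patient is one who, after a year free of OAC, "does not receive an OAC during the study period". An incident user had the same clear year and "then was prescribed an OAC during the study period".
- **Warfarin prescription duration.** The plan recognises that warfarin may be started in hospital, and says: "CPRD data do not include hospital prescribing; hence, INR test results of ≥2 will be used as a surrogate marker of exposure". Two rules put this into practice. At the start, the index date is the first prescription, or it is taken "from the date of the first INR test result above 2 if this occurs before the first issue of a prescription". At the end, there is a rule that begins "If an INR test result of ≥2 is recorded in the discontinuation period" and extends exposure to one week after the last such result.
- **Statistical analysis, Objective 1.** Cohort members are at risk for incidence up to their first OAC prescription, and person-time is cut there. The prevalence numerator counts mapped prescriptions.
- **Statistical analysis, Objective 3.** New OAC starters in each period are compared with patients not prescribed anticoagulation in that period.
- **Discussion.** Gaps in prescribing will be investigated to learn "whether patients may have been in the hospital or having their OAC prescribed elsewhere".

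**The concern.** The plan accepts that warfarin can be supplied where the database cannot see it, and that an INR of 2 or more points to exposure. It uses that information only to adjust dates in patients the practice has already prescribed for. Patients managed wholly outside the practice, for whom the surrogate is the only evidence of treatment, are left without a rule and fall by default among the untreated.

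Two results are exposed. The incidence denominator would contain person-time from people who cannot newly start anticoagulation because they are already on it. The Objective 3 no-OAC group would contain treated patients, which blurs the comparison of those started with those not started. The Discussion says the results are meant to inform the choice of confounders in later comparative studies, so that comparison will be reused.

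**Working it through.** The plan gives no figure for this point, so there is none to reproduce. The check traces one case through the rules and then illustrates the size.

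**Trace.** Take a patient aged 75 or over with AF, repeated recorded INR results of 2 or more, warfarin supplied wholly outside the practice, and no GP OAC prescription.

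1. General exposure definition (at least one prescription issued): not met.
2. Prevalent user (the Abstract requires an OAC issued in the year before entry): not met.
3. Incident user ("then was prescribed an OAC during the study period"): not met.
4. INR rule at the start: it moves the index date ahead of a first prescription. There is none, so the rule does not apply.
5. INR rule at the end: it operates in a window that opens at the expected end of the last prescription. There is none, so the rule does not apply.
6. Individual review of restarts and investigation of gaps: both need earlier prescribing, so neither reaches this patient.
7. Objective 1 incidence: there is no first prescription, so all follow-up is at-risk time.
8. Objective 3: the patient was not prescribed anticoagulation, so is a no-OAC comparator in every period contributed.

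By the surrogate, however, this patient does not satisfy "does not receive an OAC during the study period". The default classification and the surrogate disagree.

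**A related mismatch.** Where a GP prescription does follow, the warfarin section can start exposure at an earlier INR date, while Objective 1 cuts at-risk time at the first prescription. The interval between the two dates is exposed under one section and at risk under the other. The threshold itself is also written in two ways: above 2 in the index-date rule, and 2 or more elsewhere.

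**Illustration of size.** Let f be the share of at-risk person-time that is really on outside anticoagulation. The documents do not give f; 1%, 5% and 10% are assumed.

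- Denominator inflation = 1/(1 − f).
- Observed incidence / true incidence = 1 − f, with the numerator unchanged.

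For Objective 3, let f be instead the share of the no-OAC group that is really treated, and suppose these patients resemble the OAC group. For any characteristic, the observed no-OAC proportion is (1 − f) × true no-OAC proportion + f × OAC proportion. The observed difference is then (1 − f) × the true difference.

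| Assumed f | Denominator inflation | Incidence understated by | Objective 3 difference retained |
|---|---|---|---|
| 1% | 1/0.99 = 1.010 | 1% | 99% |
| 5% | 1/0.95 = 1.053 | 5% | 95% |
| 10% | 1/0.90 = 1.111 | 10% | 90% |

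If these patients do not resemble the OAC group, the last column does not apply and the distortion could go either way.

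**The case against.** **The surrogate was meant narrowly.** The sentence before it concerns treatment started in hospital and continued by the GP. Using a weak marker to adjust dates in confirmed users, but not to create users, is a coherent choice. This stands as a reason to keep the prescription-based definition as primary. It does not explain why patients the marker flags should count as untreated with no check.

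**The study is about general-practice prescribing.** The Introduction states that aim. It stands for the prevalence numerator: outside supply is not GP prescribing, and leaving it out is not an error. It does not cover the at-risk denominator or the untreated comparator.

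**INR recording is inconsistent.** The plan says so. Reclassification would depend on which practices record INR and would find warfarin but not outside DOAC supply. This stands against a change to the primary analysis and limits what a sensitivity analysis can recover.

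**The limitation is disclosed, and the article is condensed.** The Discussion admits difficulty in defining exposure, especially to warfarin. The article never says outright that INR-only patients are unexposed; that follows from its rules. But those rules are given in detail, and they produce this result.

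**Objective 1 opens by restricting its data to patients prescribed an OAC.** Read literally, this would take the traced patient out of the denominator, along with every untreated patient. The same section then puts the whole cohort at risk, and I have followed that more specific statement.

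**A stronger reading that fails.** A reader might infer that the error affects warfarin alone, understates the early periods most, and so creates an apparent rise after DOACs arrived. The documents do not support this. They do not limit outside supply to warfarin: the passages on restarting and on gaps speak of OACs generally, and DOACs have no surrogate at all. Nothing says that outside supply fell over time.

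**Conclusion.** The point holds in limited form. The rules leave patients with repeated INR results of 2 or more and no GP OAC prescription in the incidence denominator and in the Objective 3 no-OAC group, against the plan's own marker of exposure.

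The size cannot be derived from the documents. Under the assumed shares of 1% to 10%, incidence is understated by the same percentage. Objective 3 differences shrink to between 99% and 90% of their true size, provided the misclassified patients resemble OAC users. The direction of any effect on the comparison between periods is unknown. No claim is made against the prevalence estimate. This is a cheap improvement to a descriptive analysis, not a fault that invalidates it.

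**What to change.** 1. Keep the prescription-based definition as the primary analysis, and state explicitly how patients with INR of 2 or more and no GP OAC prescription are classified.
2. Report, for each of the three periods, the number of patients with two or more INR results of 2 or more (or warfarin-monitoring codes) and no GP OAC prescription.
3. Add a sensitivity analysis of Objective 1 incidence and of Objective 3. It should remove these patients from the at-risk denominator and from the no-OAC group once the criterion is met. With INR results, that is the date of the second qualifying result, so that time is not removed on the strength of a later test. Patients who do receive a GP warfarin prescription stay under the existing index-date rule. The prevalence calculation does not change.
4. Reconcile the INR-based index date with the cut of at-risk time at the first prescription, and write the INR threshold in one way.

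**Cost.** One more query on INR results and monitoring codes, data types the plan already describes; whether they have been extracted for patients without a warfarin prescription is not stated. Only some of these patients will be found, in practices that record INR; outside DOAC supply will still be missed; and a few patients whose INR was raised for other reasons will be removed. These limits should be reported with the result.
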